## Abstract

**Background:**

Unexplained Chronic Fatigue is a medical condition characterized by the presence of persistent, severe and debilitating medically unexplained fatigue, leading to impaired functioning and lower quality of life. Research suggests that physical activity can contribute to the reduction of fatigue and other somatic symptoms and can thus significantly improve physical functioning and quality of life in these patients. Based on the self-regulation (SR) theory of behaviour change, we developed a brief physical activity program for patients suffering from unexplained chronic fatigue which focuses on the training of self-regulation skills, the "4-STEPS to control your fatigue" program.

**Methods/Design:**

This is a multi-centre, randomised controlled trial (RCT) that will be carried out in local primary care centres and at the Portuguese Fibromyalgia and Chronic Fatigue Syndrome Patients Association. Patients aged between 18 and 65 and fulfilling operationalized criteria for Idiopathic Chronic Fatigue (ICF) and Chronic Fatigue Syndrome (CFS) will be recruited and randomly allocated to standard care (SC) or standard care plus a self-regulation based physical activity program (4-STEPS). Patients will be assessed at baseline, after the intervention (3 months) and at 12 months follow-up. The primary outcome is fatigue severity.

**Discussion:**

The results of the RCT will provide information about the effectiveness of a brief self-regulation intervention for promoting physical activity in patients with unexplained chronic fatigue. If the program proves to be effective, it may be considered as an adjunctive treatment for these patients.

**Trial Registration:**

ISRCTN: ISRCTN70763996

## Background

Fatigue is a common symptom in adults worldwide, being reported by around 20% of patients seeking medical care [1]. A recent epidemiological review concluded that physical activity can reduce fatigue and improve energy [1]. Recent literature emphasizes that fatigue should be considered as a multidimensional concept, incorporating both physical and mental fatigue [2]. Due to its subjective nature, fatigue is difficult to define and measure. It is a personal experience that cannot be objectively measured [3].

In most cases, fatigue is transient, but for some, fatigue symptoms become chronic, resulting in disability [4]. When fatigue lasts for at least six months, is not alleviated by rest, is debilitating, results in a significant reduction of daily activities and cannot be explained by an organic disease (unexplained chronic fatigue), it is classified as Idiopathic Chronic Fatigue (ICF) [4,5]. If ICF is accompanied by four or more of the following symptoms - unrefreshing sleep, lengthy malaise after exertion (lasting for over 24 hours), impaired memory or concentration, sore throat, tender cervical or axillary lymph nodes, muscle pain, multi-joint pain without swelling or redness and headaches of a new type or severity - it is diagnosed as Chronic Fatigue Syndrome (CFS) according to the Center for Disease Control (CDC) criteria [6].

CFS prevalence has been reported to be in between 0.2% and 2% in general population samples [7]. Prevalence rates vary according to several factors such as the criteria used to diagnose CFS [4]. In terms of prognosis, a systematic review conducted by Cairns and Hotpof [8] found that full recovery from untreated CFS is rare. It is more common for patients to experience an improvement in symptom severity. CFS etiology remains unknown [4] and it is considered to be associated with a combination of several predisposing (e.g. genes), precipitating (e.g. life events) and perpetuating (e.g. physical inactivity) factors [9].

Patients with unexplained chronic fatigue often report complaints related to exercise intolerance and post-exertional malaise [4]. Prins, van der Meer and Bleijenberg [9] considered patients' perceptions and expectations related to symptom exacerbation as a consequence of exercise, to be the main cause of the reduced levels of physical activity found in patients with unexplained chronic fatigue, rather than physical fitness limitations per se. Other studies pointed out that lack of physical activity and excessive resting are factors that result in physical deconditioning which, in turn, perpetuates fatigue and physical disability [10]. It has therefore been recommended that ICF/CFS patients engage in physical activity instead of refraining from it to manage their symptoms [10-12].

To promote physical activity in ICF/CFS, Graded Exercise Therapy (GET) has been recommended. GET is based on the assumption that in patients with unexplained chronic fatigue, physical activity must be initiated at a level that doesn't exacerbate symptoms and must be gradually increased until patients reach an optimal level of activity. Graded exercise programs follow the exercise prescription guidelines from the American College of Sports Medicine [13], tailored to each patient's level of physical activity. GET is usually delivered by an exercise physiologist or physical therapist, and consists of supervised exercise sessions and/or home-based exercise prescription (e.g. walking). Research has demonstrated that GET has a positive effect on physical activity and leads to decreased levels of fatigue [14-17].

Cognitive-behavioral therapy (CBT) has also demonstrated to be an effective treatment approach to CF. CBT interventions developed for ICF/CFS patients focus primarily on changing illness cognitions and expectations, as well as increasing control over symptoms. The CBT model makes a distinction between precipitating factors - factors that contribute to the initiation of a health problem - and perpetuating factors - factors that contribute to the maintenance of the health problem [18]. Since physical inactivity is considered to be a perpetuating factor of unexplained chronic fatigue, most CBT interventions also focus on physical activity promotion. A recent review conducted by Price and colleagues [19] concluded that CBT interventions have a positive effect on fatigue, depression and anxiety in ICF/CFS patients.

In patients with unexplained chronic fatigue a "boom and bust pattern" is frequently found, that is, a systematic alternation between periods of excessive activity (when feeling good), and, as a consequence of that, feeling extremely fatigued and having to rest for longer periods of time [20,21]. Pacing, which is having an appropriate balance between activity and rest, is considered to be an important technique for reducing fatigue symptoms. Pacing implies that patients are encouraged to set realistic goals on a daily basis in terms of activity and rest periods; it is often combined with graded exercise [22,23].

CBT uses several self-regulation (SR) techniques. SR can be defined as a sequence of actions and/or steering processes intended to attain a personal goal [24]. According to SR theory, individuals set personally important goals that guide their behavior [25]. In this goal-guidance process, self-regulation cognitions (e.g. self-efficacy expectations and autonomous/controlled motivation), emotions (positive and negative affect) and skills (e.g. self-monitoring and feedback), are considered to play an important role, both in goal setting, active goal pursuit and goal maintenance/attainment [25]. As a consequence, SR models not only contribute to our understanding of the influence of life goals on medically unexplained physical symptoms (MUPS) in general, and fatigue in particular [26], but interventions based upon these models may also encourage patients to change their personal goals from symptom avoidance to more active and positive goals [27]. In their review, Maes & Karoly [25] distinguished a number of self-regulation strategies associated with behavior change and derived a set of guidelines for interventions. These self-regulation core processes are: realistic outcome expectations; illness representations; goal setting (personal goals, ownership); planning; progress evaluation and feedback; efficacy support; attention and emotion control; control over competing goals; self-monitoring; self-reinforcement; facilitate social support; goal reformulation; relapse prevention; anticipatory coping [25].

One of the main intervention techniques using self-regulation principles is Motivational Interviewing (MI), developed by Miller & Rollnick [28]. MI is a directive, client-centered technique for eliciting behavior change, by helping clients to explore and resolve perceived conflicts (ambivalence) with respect to behavior change and analyze the discrepancies between their current behavior and their life goals and values. It aims at increasing autonomous regulation and self-efficacy (i.e. confidence in one's ability to perform a certain behavior) and promotes the transition from planning (motivational phase) to action (goal pursuit). MI has been successful in promoting physical activity in healthy populations [29], but there is limited research on MI interventions in patients with ICF/CFS and other MUPS. Powell and colleagues [30] evaluated an intervention based upon MI techniques to encourage graded physical exercise in CFS patients. The intervention led to increased physical functioning and decreased fatigue. In addition, the minimum intervention condition, consisting of only two face-to-face sessions, proved to be as successful as more extended versions of the program. A study conducted with fibromyalgia patients also showed a significant increase in physical exercise frequency, as well as reduced pain and physical impairment after an MI intervention [31].

Based on the empirical literature we developed a brief self-regulation based physical activity program for patients suffering from unexplained chronic fatigue, the "4-Steps to control your fatigue" (4-STEPS) program. In this intervention program, the combination of graded exercise and pacing is incorporated [22]. The development and evaluation of brief interventions is important because of the time, money and energy consuming efforts associated with longer interventions.

The main objective of the study is to evaluate the efficacy of the 4-STEPS program in promoting physical activity and in reducing fatigue.

## Methods/Design

### Design of the study

This is a two-arm multi-centre randomised controlled trial in patients who meet operationalised criteria for either ICF or CFS. It consists of a 3-month intervention and a 12-month follow-up phase (Figure 1). There are 3 measurement points: baseline, post-test (3 months) and follow-up at 12 months.

**Figure 1 F1:**
[figure not shown]
**Recruitment and design flow diagram**.

Approval for the trial was obtained from the Ethics Committee of the North Regional Health Administration (Ref: 27.09), from the directors of each participating health care institution and from the Portuguese Fibromyalgia and Chronic Fatigue Syndrome Patient Association.

### Setting

The trial, including measurements and intervention sessions is conducted in five Portuguese primary care centres, in a private practice clinic and at the Portuguese Fibromyalgia and Chronic Fatigue Syndrome Patient Association.

### Participants

Patients attending their physician with a main complaint of unexplained fatigue of at least six months duration are recruited for the study. Inclusion criteria are: meeting the operationalised criteria for ICF or CFS (CDC criteria) [6]; aged between 18 and 65; fluent in spoken Portuguese; capacity to provide informed consent. Exclusion criteria are: presence of a concurrent somatic condition which can explain the fatigue symptoms; patients with severe psychiatric disorders.

### Power calculation

The sample size was calculated based on the primary outcome (fatigue severity). A power calculation [32], using an independent samples t-test (5% level of significance) indicated that a sample size of 34 will have 80% power to detect a mean difference of 7 points [33,34] between the intervention and the control group, on the subjective experience of fatigue subscale of the Checklist of Individual Strength (CIS-R) [35].

Anticipating a drop-out rate of 20% [33], we aim at recruiting 41 subjects per group at baseline.

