### Randomization method

Participants are recruited from consecutive referrals and allocated to one of the two trial arms by the research team leader. Randomisation sequence is stratified by centre with a 1:1 allocation to the two treatment arms. Standard care is given to all participants and the intervention group additionally receives the 4-STEPS program.

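### 41 per group allows for about 17% drop-out, not the 20% the plan anticipates; a 20% loss corresponds to 43 per group, and the effect on power is small

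*Protocol article*

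**What the plan says.** The section Power calculation of the protocol article bases the sample size on the fatigue severity subscale of the CIS. The method is given as "using an independent samples t-test (5% level of significance"), and the result is that "a sample size of 34 will have 80% power to detect a mean difference of 7 points". The next sentence turns this into the recruitment target: "Anticipating a drop-out rate of 20% [33], we aim at recruiting 41 subjects per group at baseline".

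The section Randomization method specifies equal allocation: "Randomisation sequence is stratified by centre with a 1:1 allocation to the two treatment arms". The target is therefore 82 patients in total. The article does not show how 34 became 41, and no other section offers a different basis for 41.

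**The concern.** A drop-out rate is ordinarily a share of the patients who start. To finish with 34 after losing 20%, one divides 34 by 0.8. The printed target is instead the number obtained by adding 20% to 34, which allows for a smaller loss than the one anticipated.

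The recruitment target is the figure against which enrolment will later be judged. As printed, it implies that 80% power survives a 20% loss, and under the plan's own inputs it does not quite do so. The discrepancy flatters the design, though only slightly.

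**Working it through.** **Inputs, all from Power calculation unless noted**
- Completers needed: 34 per group. The step to 41 per group shows that 34 is a per-group number: 17 per group would inflate to 17 x 1.2 = 20.4 or 17/0.8 = 21.25, nowhere near 41.
- Anticipated drop-out: 20%.
- Target: 41 per group, 82 in total (1:1 allocation, Randomization method).
- Difference 7 points, 5% level, 80% power, independent samples t-test.
- Standard deviation and sidedness: not stated. Two-sided is assumed, and the SD is back-solved below.

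**Step 1. Reproduce the plan's figure.** 34 x (1 + 0.20) = 40.8, rounded up to 41. This matches exactly.

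**Step 2. The number that a 20% loss requires.** 34 / (1 - 0.20) = 42.5, rounded up to 43 per group, or 86 in total. Check: 43 x 0.8 = 34.4, which is enough; 42 x 0.8 = 33.6, which is not.

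**Step 3. What 41 delivers.**
- Expected completers at 20% loss: 41 x 0.8 = 32.8 per group, or 65.6 in total against the 68 needed.
- Largest loss that still leaves 34: 1 - 34/41 = 17.1%.
- If each patient independently has a 20% chance of dropping out, a group of 41 keeps at least 34 with probability of about 0.41 (binomial).
- Gap in the target: 2 per group, 4 in total (4/82 = 4.9%).

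Steps 1 to 3 need neither the SD nor the sidedness.

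**Step 4. Effect on power.** Power comes from the noncentral t distribution with 2n - 2 degrees of freedom and noncentrality (7/SD) x sqrt(n/2). With a two-sided 5% test, 34 is the smallest sufficient number per group for SDs from just under 10.0 (about 9.996) to about 10.15.

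| SD (assumed) | Power at 34 | Power at 33 | Power at 32.8 | Power at 34.4 |
|---|---|---|---|---|
| 10.0 | 81.2% | 80.0% (79.97%) | 79.7% | 81.6% |
| 10.15 | 80.0% | 78.8% | 78.5% | 80.5% |

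At the lower limit of the SD range, power at 32.8 is 79.75%. Expected power at 20% drop-out is therefore about 78.5% to 79.8%, which is about 0.3 to 1.5 percentage points below 80%. A one-sided 5% test, with its own back-solved SD of about 11.5, gives 78.7% at 32.8, so the conclusion does not depend on sidedness.

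**The case against.** The best defence is that the gap is nearly immaterial. The 20% is itself an anticipated rate taken from a cited study, 41 per group covers a loss of 17%, and at an SD of 10 the expected power is 79.7%. This stands, and it limits the point to a correction of a printed figure. A reader might infer from the arithmetic that the trial is seriously underpowered. The documents do not support that: no test or design decision changes, and the power loss is at most about 1.5 points. Nor can the loss be stated as one number, because it depends on an SD that the article does not give.

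It could be said that 20% was meant relative to completers, since 7 lost against 34 kept is 7/34 = 20.6%. The article does not define its rate that way, and a drop-out rate applied to recruited patients is the ordinary reading. It is likewise an inference, though a strong one, that 41 came from multiplying by 1.2.

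A reader might also count the unstated SD, or the missing per-group label on 34, as faults. Neither is one here: a condensed article may leave the SD to the full protocol, and the sentence that follows settles the label.

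Finally, a reader might infer that covariate adjustment makes up the loss, since the Analysis plan names AN(C)OVA. It might, but the article fixes no covariate and gives no correlation between baseline and follow-up. In any case the calculation is stated for a t-test, and adjustment would not make 41 the right allowance for a 20% loss.

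**Conclusion.** The point holds as a minor arithmetic inconsistency. The three figures 34, 20% and 41 cannot all stand: 41 per group leaves 32.8 expected completers at 20% drop-out and protects 34 only up to about 17%, while 20% corresponds to 43. This part rests only on the printed figures and on drop-out being a share of those recruited. The size of the power loss also rests on a back-solved SD of about 10.0 to 10.15 and a two-sided 5% t-test; under those assumptions, power stays within about 1.5 points of the stated 80%.

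**What to change.** Correct one sentence in Power calculation. Either of these will do:
- Keep the target and restate what it covers, for example: *41 per group allows for about 17% drop-out; at 20% drop-out about 33 per group are expected to complete, and the power of the t-test is slightly below 80%.*
- Note that a 20% drop-out allowance corresponds to 43 per group (86 in total).

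The first option needs no extra patients and costs only a slightly less favourable statement of power. If the second is adopted as the actual target, it costs 4 more patients in total. If an exact power is printed in either case, the SD behind it should be given alongside.

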### Randomization method

Participants are recruited from consecutive referrals and allocated to one of the two trial arms by the research team leader. Randomisation sequence is stratified by centre with a 1:1 allocation to the two treatment arms. Standard care is given to all participants and the intervention group additionally receives the 4-STEPS program.

### Enrolment procedure

Different procedures are followed for recruiting patients from the primary health care institutions on the one hand and from the patient association on the other.

#### Health care institutions

First, patients that meet the inclusion/exclusion criteria are approached for participation by their primary care physician. Secondly, the physician provides a brief explanation of the study to the patient and asks for the patient's authorization to be contacted by a member of the research team. Third, patients receive information from the principal investigator about the trial and what their participation involves. Finally, patients are assigned to either the intervention or the control condition by randomized sampling. All patients willing to participate sign a written informed consent before being enrolled in the study.

#### National fibromyalgia and chronic fatigue patient association

Initially, a letter containing information about the trial, what participation involves and the written informed consent form is sent to all members of the association from the Lisbon and Porto region that meet the inclusion/exclusion criteria and have previously indicated they were available for participation in research studies. Patients who wish to participate in the study return the written informed consent and are subsequently randomly assigned to either the intervention or the control group.

### Interventions

#### Control group

In addition to standard medical care, patients that are assigned to this group receive a flyer with information about the general health benefits of physical activity and the current physical activity guidelines for adults [13].

#### Intervention group

In addition to standard care, patients in the intervention group receive the 4-STEPS program that consists of:

1. Two face-to-face individual motivational interviewing (MI) sessions aimed at exploring important health and life goals, increasing participants' motivation and confidence to be physically active and setting a specific personal physical activity goal. The first MI session takes place 1 week after the baseline assessment and the second MI session takes place 2 weeks after the first. The MI session is delivered by a psychologist with MI training (member of the research team). The duration of the sessions is approximately 1 hour. Details on the topics addressed in the MI sessions are presented in Table 1.

2. Two brief telephone counseling sessions: These sessions take about 20 minutes and are provided 2 weeks and 6 weeks after the last MI session. Details on the topics addressed during the telephone sessions are presented in Table 1.

**Table 1 T1:** 4-STEPS sessions content

4-STEPS sessions	Topics
**Motivational Interviewing- Session 1**	✓ Listen to patient complaints, with emphasis on fatigue.
	✓ Illness perceptions.
	✓ Exploration of patients' present physical activity behavior.
	✓ Current health behaviors and other activities are explored (physical activity, sleep, pain, etc.).
	✓ Discussion of the information on the booklet given previously (specially the relation between CF major symptoms and physical activity behavior and boom-bust pattern).
	✓ Motivation and Confidence Scales: Exploration of the willingness to engage in physical activity (or adjust current physical activity behavior) and the confidence in one's own capability to achieve this behavior with success.
	✓ Discussion of the pros and cons (not-) to change physical activity behavior (Decisional Balance).
	✓ Social support network is addressed.

**Motivational Interviewing- Session 2**	✓ Exploration of possible competing goals with physical activity (e.g. housework chores) and link to core values.
	✓ Strategies to overcome obstacles to physical activity and competing goals are addressed.
	✓ Based on the register of daily activities and steps taken (pedometer register) and GET scheme for physical activity, the patient establishes a personal physical activity goal for the following two months.
	✓ Discuss the possible reasons for perpetuation of symptoms and difficulty to change health behaviors in CF patients, namely perfectionism, fear of movement, presence of stressful situations and boom-bust pattern. (some are already mentioned at the first motivational interview and are now emphasized).
	✓ Exploration of emotion control importance and techniques (e.g. relaxation techniques).

**Telephone sessions:**	✓ Revision of the physical activity goal planning (adequacy to the patients' present situation).
	✓ Relapse prevention (strategies to overcome new or persisting difficulties to physical activity and emotion control strategies).

3. Self-regulation (SR) booklets: There are two booklets that are designed to help patients change their level of physical activity (Informational booklet and Workbook). The Informational booklet is provided at the end of the baseline assessment, the "Step 1" part of the Workbook is provided at the first MI session and the parts "Step 2", "Step 3" and "Step 4" are given during the second MI session. Details on the topics that are addressed in the SR booklets are presented in Table 2.

4. A pedometer to register physical activity on a daily basis (steps taken) during the 3 month intervention period. Instructions on how to use the pedometer are given in the baseline assessment session (Table 2).

5. Daily activities record (Table 2): Patients receive several daily activity records (physical activities, mental activities and rest). The first daily activity record is given to the patient at the end of the first MI session; patients are asked to fill out the activity record in the time period between the first and second MI session. This homework assignment aims at evaluating the patients' daily activities management and possibly recognizing an erratic pattern of rest and activity (boom and bust cycle). At the end of the second MI session, patients receive daily activities records that can be used to monitor changes in daily activity patterns during the subsequent nine weeks.

6. Leaflet for family (Table 2): At the end of the first MI session patients receive a leaflet for their partner or significant other in order to increase social support.

**Table 2 T2:** 4-STEPS Materials content

4-STEPS materials	TOPICS
**Self-regulation Informational booklet**	✓ Overview of Chronic Fatigue: CDC diagnosis criteria, epidemiology information, etiology, possible factors that contribute to a better or words prognosis (e.g. physical inactivity/activity).
	✓ Physical activity: current physical activity guidelines for adults in general population, physical and psychological benefits of physical activity, benefits of physical activity for CF. Information about different types of physical activities (that are appropriated for CF) such as walking as well the importance and illustration of relaxation training.
	✓ Link between CF symptoms and physical (in-) activity (deconditioning cycle) and boom-bust pattern (erratic pattern of rest and activity).

**Self-regulation Workbook**	*STEP 1 - "Am I ready to start?"*
	✓ Motivation and Confidence Scales: Patients' willingness and confidence to do adjusted levels of physical activity is assessed on a scale for ranging from 0% (not at all) to 100% (very much).
	✓ Decisional Balance: list of the pros and cons (not-) to change in relation to physical activity.
	✓ Competing goals with exercise: information on the importance o analyzing possible competing goals (or conflicting activities) with exercise that may be refraining patients from physical activity. List of two main activities (e.g. other leisure activities).
	✓ Activity/Rest Diary and Pedometer log - instructions to use for two weeks (interval between MI sessions) and the importance of the pedometer as a motivational strategy.
	*STEP 2 - "My physical activity goal":*
	✓ GET Scheme and daily activity management: information on the importance of increase physical activity level gradually, consider the way patients feel in different days (different levels if patients is feeling good or bad), importance of rest during physical activity, importance of adjusting physical activity levels to the amount of effort spent in that day (balance between activities and rest).
	✓ Goal setting activity: explanation of how to set a goal (SMART - specific, measurable, achievable, realistic and timely), formulation of a personal physical activity goal to achieve in 2 months time (e.g. to do brisk walking four days per week for 30 minutes (plus 10 minutes break), implementation intentions (type of activity, frequency and intensity, period of the day, with whom, where) and a goal ladder (patients formulate goals for every 2 weeks until reaching the two months time and main goal.
	✓ Information on self-rewarding for each step goal achieved.
	✓ Tips for managing daily activities and incorporate physical activity on the daily routine
	*STEP3 - "Overcoming obstacles":*
	✓ Problem solving activity: List two main physical activity barriers and a strategy to overcome it.
	*STEP 4 - "I am physically active...and I want to keep that way":*
	✓ Relapse prevention information and strategies
	*Resources and support for CF and physical activity*.

**Pedometer Record**	✓ Similar to the record used for the assessment (day of the week and number of steps for each day).
**Daily activities record**	✓ Record containing the days of the week and hours each day. Patients fill the activities they do in each hour of day. The options are: physical activities, other activities (activities requiring mental effort) and rest. Each option is explained in detail.

**Leaflet for family**	✓ Facts about CF.
	✓ Brief information on the relation between physical activity and CF.
	✓ Tips for partners or other relatives to support patients with CF.

